## Abstract

**Objective:**

Type 2 diabetes mellitus (T2DM) induces integrated cardiovascular and metabolic impairments. The comprehensive effect of aerobic exercise on these systemic alterations remains unclear. Therefore, we designed a randomized controlled trial to investigate its impact on integrated cardiovascular health — specifically assessed by nitroglycerin-mediated dilation (NMD) and myocardial global work efficiency (GWE) — and systemic energy metabolism in patients with T2DM.

**Methods:**

This study is a randomized, single-assessor-blind, parallel-group, two-arm controlled trial that will enroll 74 patients with T2DM. Participants will be randomly assigned in a 1:1 ratio to either a 12-week supervised aerobic exercise group (55–75% of HR_peak_, three times per week) or a non-exercise control group. The primary outcomes are the changes from baseline to 12 weeks in NMD and GWE. Secondary outcomes include key cardiometabolic indicators (energy metabolism, insulin levels), office and 24-hour ambulatory blood pressure, cardiovascular risk factors, 24-hour movement behavior, cardiopulmonary function, arterial stiffness (baPWV), vascular endothelial function (FMD), cardiac electrical activity, echocardiographic parameters, and self-reported fatigue. Additional exploratory variables include markers of myocardial injury and skeletal muscle injury, circulating markers of oxidative stress and inflammation, central fatigue biomarkers, and levels of cardiovascular-related hormones. Recruitment began in June 2025 and is currently ongoing.

**Discussion:**

This study provides an integrated physiological perspective on how 12-week moderate-intensity aerobic exercise influences cardiovascular function and systemic metabolism in patients with T2DM. We hypothesize that 12 weeks of aerobic exercise will significantly improve NMD and GWE, concurrent with enhanced metabolic flexibility and reduced fatigue compared to the non-exercise control group.

## Introduction

1

Type 2 diabetes mellitus (T2DM) is a metabolic disorder characterized by insulin resistance, which leads to impaired glucose metabolism and a subsequent loss of metabolic flexibility (1). Cardiovascular disease is the leading cause of morbidity and mortality among patients with T2DM (2–4). Through mechanisms including metabolic dysregulation, oxidative stress, and inflammation, T2DM induces pathological remodeling and functional impairment of the cardiovascular system (5). Patients with T2DM frequently present with significant diastolic dysfunction and autonomic imbalance, accompanied by myocardial hypertrophy and fibrosis, which are hallmarks of adverse myocardial remodeling (6). Furthermore, T2DM can induce myocardial metabolic inflexibility, leading to dysregulated energy metabolism that accelerates cardiac dysfunction (7). In this context, myocardial Global Work Efficiency (GWE) serves as a sensitive and early indicator for assessing myocardial energetics (8). Vasculopathy is another common complication of T2DM. Patients frequently exhibit increased arterial stiffness, pathological vascular remodeling, and impaired endothelium-dependent vasodilation (9). Notably, as research has confirmed the prevalence of vascular smooth muscle dysfunction in T2DM, Nitroglycerin-Mediated Dilation (NMD) is employed to specifically evaluate vascular smooth muscle function. These changes contribute to the dysregulation of peripheral resistance and an elevated risk of atherosclerosis (10). Consequently, the pathological crosstalk between cardiac and vascular abnormalities in T2DM leads to a significant elevation in systolic blood pressure (SBP), ultimately disrupting blood pressure homeostasis (11). This underscores the systemic damage that T2DM imposes on the cardiovascular system as a whole. Furthermore, accumulating evidence indicates that patients with T2DM commonly exhibit reduced peak oxygen uptake (VO_2peak_). As an integrative measure of the coordinated function of the cardiovascular, respiratory, and musculoskeletal systems, VO_2peak_ is the strongest predictor of integrated cardiovascular function in this population (12, 13). From the perspective of integrative physiology, dysfunction in a single organ system inevitably compromises overall systemic function. This suggests that T2DM induces pathological inter-organ interactions via shared mechanisms, resulting in global cardiovascular dysfunction rather than isolated organ damage. Therefore, the focus of therapeutic interventions for T2DM should expand from targeting single organs to enhancing integrated physiological function to achieve more comprehensive clinical benefits.

Aerobic exercise (AE) is a well-established non-pharmacological intervention for improving cardiovascular health and ameliorating metabolic abnormalities, and it is clinically recommended as a cornerstone of T2DM management. Specifically, AE has been shown to enhance insulin sensitivity and improve glucose metabolism (14). In addition, AE can attenuate T2DM-induced cardiovascular remodeling and functional impairments (15). However, existing studies have primarily focused on the effects of AE on individual cardiovascular organs or isolated metabolic pathways. There is limited evidence regarding its impact on integrated cardiovascular function and systemic metabolism. Thus, there is a compelling need to investigate the role of AE in promoting integrative physiological function in this population.

Although regular AE can improve metabolic and cardiovascular health in patients with T2DM, it is noteworthy that this population generally has insufficient levels of physical activity (PA) (16). Low PA can trigger a cascade of adverse physiological responses, including impaired energy metabolism, decreased insulin sensitivity, reduced exercise tolerance, and increased cardiovascular disease risk, thereby perpetuating or exacerbating the pathological progression of T2DM (17). The reasons for insufficient PA among individuals with T2DM are multifactorial, with fatigue being recognized as a key contributor. The pathogenesis of fatigue is complex, involving disturbances in energy metabolism, oxidative stress, and inflammation (18). Specifically, fatigue in this population manifests through both central and peripheral pathways: centrally, it involves disturbances in neurotransmitter balance, while peripherally, it is characterized by skeletal muscle injury and oxidative stress. While regular AE has been shown to alleviate fatigue in patients with T2DM, the underlying mechanisms remain unclear, and most studies have lacked objective biomarkers to quantify fatigue.

We hypothesize that a 12-week moderate-intensity aerobic exercise intervention will significantly enhance integrated cardiovascular function, specifically by improving GWE and NMD, while concurrently restoring systemic energy metabolism and metabolic flexibility in patients with T2DM. Furthermore, regarding the mechanisms of fatigue alleviation, we hypothesize that aerobic exercise will mitigate fatigue via a dual pathway: centrally, by modulating the balance of neurotransmitters (including serotonin, dopamine, and GABA), and peripherally, by reducing skeletal muscle injury biomarkers (CK and Myoglobin) and oxidative stress.

## Materials and methods

2

### Research design

2.1

This study is a single-assessor-blind, parallel-group, two-arm randomized controlled trial. Participants will be randomly assigned in a 1:1 ratio to either a 12-week aerobic exercise group (AE group) or a non-exercise control group (Con group). Clinical assessments will be performed at baseline (pre-intervention) and at the 12-week follow-up. A detailed schedule of enrollment, interventions, and assessments is presented in **Table 1**. Considering the minimum clinically effective dose of exercise, adherence to the intervention will be defined as the completion of at least 80% of the prescribed exercise sessions. Participants who do not meet this threshold will be categorized as non-adherent. To minimize attrition bias, all participants, regardless of their adherence or completion of the intervention, will be followed up and included in the primary analysis according to the intention-to-treat (ITT) principle. Written informed consent will be obtained from all participants before enrollment. The reporting of this trial will adhere to the Consolidated Standards of Reporting Trials (CONSORT) statement.

**Table 1 T1:** Participant timeline: schedule of enrollment, interventions, and assessments.

Trial period	Enrollment		Post-randomization			Close-out
Timepoint	Screening *(Day-12 to 0)*	Baseline *(Day0)*	Intervention Period *(Weeks 1-6)*	Intervention Period *(Day42)*	Intervention Period *(Weeks 6-12)*	*Week 12 (± 3 days)*
Enrollment:						
Eligibility screen	X					
Informed consent	X					
Medical history	X					
Randomization		X				
Intervention:						
Aerobic Exercise Group		X				X
Control Group		X				X
Assessments:						
Primary outcomes						
nitroglycerin-mediated dilation		X				X
myocardial global work efficiency		X				X
Secondary outcomes						
Energy Metabolism		X				X
Peak Heart Rate (HR_peak_)		X		X		X
Traditional Cardiovascular Risk Factors		X				X
Cardiovascular & Cardiopulmonary Function		X				X
Self-reported fatigue assessment		X				X
24-hour physical activity monitoring		X				X
Circulating biomarkers		X				X
Safety monitoring						
Adverse Events		X				X

### Research setting

2.2

A total of 74 participants with T2DM will be recruited from local communities in Shenyang, China in collaboration with community physicians. Recruitment strategies will include the distribution of posters, flyers, brochures, and health education lectures. Clinical physicians will confirm the diagnosis and assess eligibility for all potential participants. The exercise intervention will be conducted at a fitness and rehabilitation center, while all clinical assessments will take place at a partner hospital and associated laboratories. Baseline and follow-up assessments will be conducted by trained research staff who are blinded to group allocation, and the exercise intervention will be supervised by certified clinical exercise physiologists. Participant recruitment commenced in June 2025. The study execution period is from June 30, 2025, and is currently ongoing (**Figure 1**).

**Figure 1 f1:**
[figure not shown]
Flowchart of study procedures.

### Inclusion criteria

2.3

Participants will be eligible for inclusion if they meet the following criteria: (1) diagnosed with T2DM according to the American Diabetes Association (ADA) guidelines (19); (2) aged between 50 and 65 years; (3) a disease duration of 1 to 10 years, with a stable medication regimen (including glucose-lowering agents, antihypertensives, and statins) for at least 3 months prior to enrollment; (4) HbA1c levels between 6.5% and 11.0%; (5) absence of regular exercise habits, defined as performing less than 150 minutes of moderate-intensity physical activity per week and being categorized as having a “Low” physical activity level according to the International Physical Activity Questionnaire (IPAQ) scoring protocol; (6) ability and willingness to voluntarily participate in the exercise intervention; and (7) provision of written informed consent.

### Exclusion criteria

2.4

Participants will be excluded from the study if they meet any of the following criteria: (1) cognitive impairment; (2) severe comorbidities or complications such as heart failure, autonomic neuropathy, or stroke; (3) musculoskeletal disorders causing exercise limitation; (4) history of malignancy; (5) allergy to nitroglycerin; (6) hypotension; (7) glaucoma; or (8) end-stage renal disease.

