Participants assigned to the control group (Con group) will not receive any supervised or structured exercise intervention. To ensure a clear distinction from the AE group, they will be explicitly instructed to maintain their habitual lifestyle patterns throughout the 12-week study period. To objectively monitor adherence to these instructions, physical activity levels will be assessed weekly using the International Physical Activity Questionnaire (IPAQ). Any deviations from baseline activity patterns will be documented.

Throughout the 12-week intervention, all participants will be required to maintain their baseline medication regimens. Dosage adjustments will be permitted only when medically necessary for safety reasons (e.g., in cases of severe hypoglycemia or uncontrolled blood pressure), and any such modifications will be meticulously documented.

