### Measurement

2.8

Comprehensive clinical assessments—including metabolic, cardiovascular, cardiopulmonary, fatigue, and skeletal muscle tests—will be performed at baseline and at the 12-week follow-up. With the exception of the oral glucose tolerance test and associated 2-hour postprandial glucose measurement, all assessments will be conducted in the morning after a minimum 12-hour overnight fast. Participants will be instructed to abstain from alcohol, caffeine for 24 hours and withhold their morning medications on the day of assessment to minimize pharmacological interference. To mitigate the confounding effects of acute exercise, post-intervention assessments will be scheduled 48 hours after the final training session. For biochemical analyses, venous blood samples (approximately 6 mL) will be drawn from an antecubital vein into serum separation tubes. The tubes will be gently inverted and then allowed to clot at room temperature for 30–60 minutes. The samples will then be centrifuged at 3000 rpm for 10 minutes at 4°C, and the resulting serum will be aliquoted and stored at –80°C until analysis. To minimize inter-assessor and instrument variability, all measurements will be performed by the same trained technician using the same equipment at both time points.

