#### Vascular smooth muscle function

2.10.1

Vascular smooth muscle function will be assessed using the same ultrasound device (unexp18g, UNEX, Japan) following a procedure similar to that of the FMD test. After at least 15 minutes of rest, participants will receive 75 µg of sublingual nitroglycerin, and the maximal dilation of the same brachial artery segment will be measured. NMD will be calculated using the formula:

$$\text{NMD\%}=\frac{\text{maximal post-nitroglycerin diameter }-\text{ baseline arterial diameter}}{\text{baseline arterial diameter}}\times 100\%.$$

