### Statistical analysis

2.12

All statistical analyses will be performed using R software (version 4.3.1 or later; R Foundation for Statistical Computing, Vienna, Austria). For the description of baseline data, normally distributed continuous variables will be presented as 
mean±standard deviation (SD), while non-normally distributed variables will be reported as median [interquartile range (IQR)]; categorical variables will be expressed as frequencies and percentages (n, %). For the comparison of baseline data between groups, independent samples t-tests will be used for normally distributed continuous variables, the Mann-Whitney U test will be used for non-normally distributed data, and the chi-square (χ²) test or Fisher’s exact test will be used for categorical data.

Efficacy analyses will be conducted according to the intention-to-treat (ITT) principle and will include all randomized participants. Continuous outcomes, including NMD and GWE, will be analyzed using linear mixed-effects models (LMMs). To rigorously control for potential confounding, background medication use will be prespecified and included as fixed-effect covariates in the models. Medications will be categorized by therapeutic class, with binary indicators (yes/no) created for: (1) glucose-lowering agents (with separate indicators for GLP-1 receptor agonists and SGLT2 inhibitors), (2) antihypertensive medications, and (3) statins. Each LMM will incorporate group, time, and the 
group×time  interaction as fixed effects, with a random intercept for each participant to account for repeated measurements.

Sensitivity analyses will be performed using multiple imputation to assess the robustness of the findings under different assumptions regarding missing data. In addition, a per-protocol (PP) analysis will be conducted as a secondary sensitivity analysis, including only participants with an attendance rate of at least 80%. Secondary outcomes will be considered exploratory and hypothesis-generating; therefore, no adjustment for multiple comparisons will be applied. A two–tailed *P*–value < 0.05 will be considered statistically significant.

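### The exclusion criteria screen for nitroglycerin allergy, hypotension and glaucoma but not for current use of organic nitrates or PDE5 inhibitors, although nitroglycerin is given at baseline and Week 12

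*Protocol article*

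**What the plan says.** Section 2.10.1 of the protocol article describes the NMD test: after rest, participants receive 75 µg "of sublingual nitroglycerin, and the maximal dilation of the same brachial artery segment will be measured". Table 1 schedules NMD at baseline and at Week 12, so a participant who completes the trial is dosed twice.

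Section 2.4 prints eight numbered exclusions, the last four being "5) allergy to nitroglycerin; (6) hypotension; (7) glaucoma; or (8) end-stage renal disease". Criterion (2) is worded more openly: "severe comorbidities or complications such as heart failure, autonomic neuropathy, or stroke".

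On medication, section 2.3 requires "a stable medication regimen (including glucose-lowering agents, antihypertensives, and statins) for at least 3 months prior to enrollment", and section 2.7 has participants stay on their baseline regimen: "Dosage adjustments will be permitted only when medically necessary for safety reasons". Section 2.8 tells participants to "withhold their morning medications on the day of assessment to minimize pharmacological interference".

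On screening, section 2.2 states: "Clinical physicians will confirm the diagnosis and assess eligibility for all potential participants". Table 1 adds a medical history at the screening visit. Section 2.9 requires a health screen before each training session or CPET.

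**The concern.** Three of the listed exclusions (allergy, hypotension, glaucoma) are natural precautions for a nitroglycerin challenge, so the authors evidently considered who should not receive the drug. The list has no drug-interaction criterion. As general pharmacology, which the article does not state, organic nitrates and PDE5 inhibitors can both add to nitroglycerin's blood-pressure-lowering effect. The protocol already treats low blood pressure as a reason not to enrol.

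What is at stake is the safety of a small, unknown number of participants during a research procedure. The validity of the NMD comparison is not in question.

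**Working it through.** **Does any stated rule bar a user of either class from the nitroglycerin dose?** This is a check of the text, taking each relevant rule in turn.

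- *Exclusion list (2.4).* None of the eight items names either class. A physician could use criterion (2) to exclude someone whose cardiac disease requires nitrates, although angina and coronary disease are not among its examples. It does not naturally reach a PDE5-inhibitor user without severe comorbidity.
- *Stable regimen (2.3) and maintained medication (2.7).* These require stability and continuation. A stable user meets both.
- *Physician eligibility review (2.2) and medical history (Table 1).* Use may come to light here, but the printed criteria do not say what to do about it.
- *Morning-medication hold (2.8).* This covers doses due on the morning of the visit. It does not reach an evening, on-demand or long-acting dose.
- *Health screen (2.9).* It is tied to training sessions and CPET. The NMD test is not named.
- *Medication indicators (2.12).* "Medications will be categorized by therapeutic class, with binary indicators (yes/no) created for" introduces glucose-lowering agents, antihypertensives and statins. Neither class has its own indicator. This shows only that the analysis section does not identify such users either; the point does not depend on it.

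No stated rule bars the dose.

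**What would the remedy cost in NMD power?** These figures size the fix, not the harm.

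Inputs from section 2.5: δ = 4.0, σ = 5.6, two-sided α = 0.05, 32 per group required, 10% dropout, 37 per group recruited. The standardized effect is 4.0/5.6 = 0.714. Power is for a two-sample t-test with noncentrality 0.714/√(1/n₁ + 1/n₂) and n₁ + n₂ − 2 degrees of freedom.

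The plan's own figure first: at 32 per group the noncentrality is 2.857 on 62 degrees of freedom and power is 0.803, which agrees with the stated requirement of 32. After dropout, 37 × 0.9 = 33.3, or 33 per group.

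| Evaluable for NMD | Situation | Power |
|---|---|---|
| 37 and 37 | all recruited | 0.858 |
| 33 and 33 | after 10% dropout | 0.815 |
| 33 and 32 | one further value missing | 0.809 |
| 32 and 32 | two further values missing | 0.803 |
| 32 and 31 | three further values missing | 0.797 |

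The article gives no prevalence of use. Assuming 1% to 5% of participants use either class, that is 74 × 0.01 = 0.74 to 74 × 0.05 = 3.7 people. This counts users. It does not count people with active drug at the challenge, or events. It overstates the missing values the fix would create, because users found before randomization would not be enrolled.

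**The case against.** The strongest reply is that this is an omission from a condensed article. Pre-dose checks and drug-by-drug contraindications often sit in the full protocol, and nothing printed here is false or contradictory. That limits the point: a reader might infer that the trial has no pre-dose check at all, and the article cannot support that. What stands is narrower. The article prints a specific list that already contains nitroglycerin precautions, and that list can be judged as printed.

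Second, the harm rests on general pharmacology and is not quantified. That is correct. Nothing in the article shows that 75 µg is hazardous in this population, and the power figures must not be read as evidence of severity.

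Third, the safeguards overlap. Physician review, medical history, the hypotension and comorbidity exclusions and the morning hold together leave a narrow residual: a user not stopped at review whose dose is still active at the test. The DSMB also adjudicates adverse events, though only after they occur. This lowers the likelihood without closing the gap.

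Fourth, a reader might infer that nitrate tolerance or a potentiated response biases the co-primary NMD result. The article gives no basis for a material effect. Stable use largely cancels in the change from baseline, and randomization spreads users across the arms.

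Fifth, a remedy can itself be loose. Section 2.4 gives no numeric definition of hypotension, and the brachial readings in section 2.11.7 precede echocardiography but are not said to precede the nitroglycerin dose. A pre-dose check therefore needs its own threshold and its own reading.

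**Conclusion.** The point holds as a modest patient-safety improvement. As printed, the criteria would allow a stable user of organic nitrates or PDE5 inhibitors to be enrolled and given nitroglycerin at both visits, and the section 2.9 screen does not cover that dose. The size of the risk cannot be derived from the article; the low dose and the existing safeguards reduce it.

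The conclusion rests on two things: the criteria as printed, and the general pharmacological premise of an additive fall in blood pressure. No material effect on the NMD comparison is claimed, and nothing is claimed about what the full protocol contains. The change is worth making because it is specific and cheap and because recruitment is still open, so it can protect new enrollees and those awaiting Week 12. Confidence is medium.

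**What to change.** **Eligibility.** Add to section 2.4: *current use of organic nitrates, or PDE5-inhibitor use within a drug-specific interval set by the trial clinicians*.

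**Before each nitroglycerin dose.** Extend the section 2.9 health screen to the NMD test at both visits. Ask about use of either class, which also catches drugs started after enrolment, and take a blood-pressure reading against a numeric threshold that the trial clinicians fix in advance.

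**Handling.** Randomization follows the baseline assessments (section 2.6), so a user found at baseline is a screen failure and no randomized participant is lost. If a randomized participant has used either class at Week 12, reschedule NMD within the ±3-day window where the interval allows. Otherwise omit the challenge and record NMD as missing with the reason. In either case collect GWE and all other outcomes, so that the participant stays in the ITT analysis.

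**Cost.** A short amendment, plus one question and one blood-pressure reading per dose; slightly more screening, a few fewer eligible people and possibly one or two missing NMD values. On the section 2.5 assumptions, two missing values beyond 10% dropout keep power just above 80%; a third takes it just below. Rescheduling also moves the test away from the 48-hour interval after the last training session (section 2.8), and only in the exercise arm, so the time since that session should be recorded.
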